## Abstract

**Background:**

Facial mutilation and deformities can be caused by cancer, tumours, injuries, infections, and inherited or acquired deformities and has the potential to degrade one’s quality of life by interfering with fundamental tasks like communication, breathing, feeding, and aesthetics.

Depending on the type of defect, producing maxillofacial prostheses for the rehabilitation of patients with various defects can be challenging and complex. The prosthesis is used to replace missing or damaged parts of the cranium and face, like the nose, auricle, orbit, and surrounding tissues, as well as missing areas of soft and hard tissue, with the primary goal of increasing the patient’s quality of life by rehabilitating oral functions such as speech, swallowing, and mastication.

Traditional maxillofacial prosthesis impression and fabrication processes include a number of complicated steps that are costly, time-consuming, and uncomfortable for the patient. These rely on the knowledge of the maxillofacial team, dental clinicians, and maxillofacial technician.

The foundation of the impression is the keystone for creating a prosthesis. However, this is the most time-consuming and difficult chair-side operation in maxillofacial prosthesis manufacturing since it requires prolonged interaction with the patient. The field of prosthesis fabrication is being transformed by the digital revolution. Digital technology allows for more accurate impression data to be gathered in less time (3 to 5 min) than traditional methods, lowering patient anxiety. Digital impressions eliminate the need for messy impression materials and provide patients with a more pleasant experience. This method bypasses the procedure of traditional gypsum model fabrication. This eliminates the disparity caused by a dimensional distortion of the impression material and gypsum setting expansion. Traditional dental impression processes leave enough room for errors, such as voids or flaws, air bubbles, or deformities, while current technology for prosthesis planning has emerged as an alternative means to improve patient acceptability and pleasure, not only because the end result is a precisely fitted restoration but also because the chair-side adjustments required are reduced.

The most frequent approaches for creating 3D virtual models are the following. To begin, 3D scanning is employed, in which the subjects are scanned in three dimensions, and the point cloud data is used to create a virtual digital model.

**Methods:**

It will be a hospital-based randomised control trial, carried out at the Department of Prosthodontics, Sharad Pawar Dental College, Sawangi (Meghe), Wardha, a part of Datta Meghe Institute of Medical Sciences (Deemed University). A total of 45 patients will be selected from the outpatient department (OPD) of the Department of Prosthodontics. All the patients will be provided written consent before their participation in the study.

**Methodology:**

1. Patient screening will be done, and the patient will be allocated to three techniques that are the conventional manual method, photogrammetry method, and 3D scanning in a randomised manner

2. The impression of the defect will be recorded by conventional manual method, photogrammetry method, and 3D scanning

3. The defect will be modelled in three ways: first is as per the manual dimension taken on the patient, second is the organisation of photographic image taken with lab standards and third is plotting of point cloud data to generate the virtual 3D model

4. For photogrammetric prosthesis design, finite photos/images will be taken at multiple angles to model the 3D virtual design. With the use of minimum photographs, the 3D modelling can be performed by using freeware, and a mould is obtained

5. The CAD software was used to design the prosthesis, and the final negative mould can be printed using additive manufacturing

6. The mould fabricated by all three methods will be analysed by a software using reverse engineering technology

**Study design**: Randomised control trial

**Duration**: 2 years

**Sample size**: 45 patients

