The most frequent approaches for creating 3D virtual models are the following. To begin, 3D scanning is employed, in which the subjects are scanned in three dimensions, and the point cloud data is used to create a virtual digital model.

Photogrammetry is the second method, which uses finite pictures taken from various perspectives to create 3D digital models. When compared to traditional data collection methods, the two methods are non-contact and save time. Though 3D scanning is a quick and accurate process, it has drawbacks such as a high set-up cost and the need for expert labour. Because of these drawbacks, this technology is only used in prosthetic design on a very limited basis. With a little compromise in 3D modelling accuracy, the photogrammetry method can overcome the drawbacks of 3D scanning. It primarily offers advantages such as the usage of freeware for model creation, the ability to handle the method with semi-skilled people, and the ability to produce good results even with a phone camera using standard operating procedures [4].

The initial step in the photogrammetry approach is to collect photos from all angles; after that, post-processing can be done by a professional using photogrammetry software and CAD/CAM tools. The photogrammetrically formed 3D model can then be used to create a mould, which can be compared against moulds fabricated via 3D scanning and traditional methods [5].

Because the prosthodontist may review the digitally scanned impression at the chairside just by magnifying it, any problems can be corrected before the data is sent to the dental laboratory [6]. However, the complete manufacture of the prosthesis using rapid prototyping is expensive, and the final prosthesis creation is fully dependent on the donor anatomy [7].

When compared to a manually modelled prosthesis, a 3D-produced prosthesis made from the mirror image of the undamaged portion or from the donor does not provide improved aesthetics. The art of sculpturing and adding uniqueness into the prosthesis can be added using the traditional wax-up procedure [8]. Other laboratory procedures can be done using the traditional way to keep costs down and make the prosthesis more appealing [9–11]. 

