### Sample size {14}

45 Daniel formula for sample size calculation$$n=\frac{Za/{2}^2\cdot P\cdot \left(1-P\right)}{d^2}$$where*Zα*/2^2^ is the level of significanceAt 5%, i.e. 95% confidence interval = 1.96*P* = prevalence of craniomaxillofacial defects = 3% = 0.03*d* = desired error of margin = 5% = 0.05$$n=\frac{1.96^2\times 0.03\times \left(1-0.03\right)}{0.05^2}=44.71$$*n* = 45 patients needed for the study

Study reference: Mohamed Khallaf et al.

Formula reference: Daniel et al.

Statistical method: chi-square test, one-way ANOVA, Tukey multiple comparison test

Software used: SPSS 27.0 V and Graph Pad Prism 7.0V

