### Procedure for unblinding if needed {17b}

Data analysis from spreadsheets of random numbers was done to determine the assignment; there is no human involvement; and the process is fully concealed from both study investigators and prospective participants until the study arm is assigned.

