### Methods for additional analyses (e.g. subgroup analyses) {20b}

#### SPIRIT guidance: methods for any additional analyses (e.g. subgroup and adjusted analyses)

As there are no subgroups in the study, the subgroup analysis will not be carried out. The population will be studied under three groups—conventional impression, 3D scanning, and photogrammetry—so there is no role of subgroups.

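### The protocol describes both one method per patient and all three methods on each defect, and the named independent-groups tests suit only the first

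*Protocol article*

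**What the plan says.** All references are to the protocol article.

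**One method per patient.** Step 1 of the methodology (Abstract, and Study setting {9}) allocates the patient among the three techniques at random. Implementation {16c} has participants assigned to interventions. Procedure for unblinding {17b} describes concealment "until the study arm is assigned". The additional-analyses section {20b} states: "The population will be studied under three groups—conventional impression, 3D scanning, and photogrammetry".

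**All three methods on one defect.** Step 2 reads: "The impression of the defect will be recorded by conventional manual method, photogrammetry method, and 3D scanning". Step 3 begins: "The defect will be modelled in three ways". Both steps are repeated in the biological-specimens section {33}.

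**Fits either reading.** Step 6: "The mould fabricated by all three methods will be analysed by a software using reverse engineering technology". Intervention description {11a} says that the photogrammetric model "can then be used to create a mould, which can be compared against moulds fabricated via 3D scanning and traditional methods".

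**Tests.** Sample size {14} lists "chi-square test, one-way ANOVA, Tukey multiple comparison test". Statistical methods {20a} lists chi-square and Student's t-test at the 0.05 level, without saying whether the t-test is paired. No repeated-measures or mixed-model method is named.

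**The concern.** These are two different trials. In one, 45 patients give 45 independent observations, one per patient. In the other they give 135 correlated observations, 45 per method. The unit of analysis and the standard error of every method comparison depend on which trial is run. Staff following step 1 would take one impression per patient; staff following steps 2 and 3 literally would take three.

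The named tests assume independent groups. If the recordings are made as steps 2 and 3 say and the data are analysed as listed, the standard errors are wrong for the comparison of accuracy that the fourth objective sets. How many impressions each patient undergoes is a matter of trial conduct, so a separate analysis plan could not settle it.

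**Working it through.** **1. The stated sample size.** Inputs from Sample size {14}: z = 1.96, P = 0.03, d = 0.05.

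n = 1.96² × 0.03 × 0.97 / 0.05² = 44.716, rounded up to 45. The stated figure reproduces. The formula estimates a single proportion. It has no term for arms, repeated measurements or correlation, so it cannot show which design was meant.

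**2. The passages side by side.**

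| Place | One method per patient | All three per patient |
|---|---|---|
| Step 1 | natural reading | strained |
| {16c}, {17b}, {20b} | yes | no |
| Step 2 (methods joined by *and*, one defect) | only if read as a list across arms | literal reading |
| Step 3 (one defect, three models) | only if read as a list across arms | literal reading |
| Step 6, {11a} | compatible | compatible |

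No sentence limits steps 2 and 3 to the allocated method, and none says that every patient receives all three.

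**3. Effect on the tests if all three are recorded per patient.** The protocol gives no within-patient correlation ρ, SD or effect size. The values of ρ (0.3, 0.5, 0.7) and the effects below are assumptions, in units of a common SD σ. The test is taken as two-sided 5%, which the 1.96 in {14} implies.

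For two methods measured on the same n patients:

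- true variance of the mean difference: 2σ²(1−ρ)/n
- variance that an unpaired test assumes: 2σ²/n
- the unpaired standard error is therefore too large by the factor 1/√(1−ρ)
- under no difference the unpaired statistic has SD √(1−ρ), so the real type I error is 2·P(Z > 1.96/√(1−ρ))

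| ρ | SE factor | 1.96/√(1−ρ) | real type I error |
|---|---|---|---|
| 0.3 | 1.20 | 2.343 | 1.9% |
| 0.5 | 1.41 | 2.772 | 0.56% |
| 0.7 | 1.83 | 3.578 | 0.03% |

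**4. Power at a 0.5 SD difference, n = 45, ρ = 0.5.**

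- Unpaired: the statistic has mean 0.5 × √(45/2) = 2.372 and SD √0.5 = 0.707. Power = P(Z > (1.96 − 2.372)/0.707) = P(Z > −0.582) = 72%. Simulation of the t-test itself (40,000 runs) gives about 70–71%.
- Paired: the noncentrality is 0.5 × √45 / √(2 × 0.5) = 3.354 on 44 degrees of freedom. Power = 91%.

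**5. One-way ANOVA over all three methods.** Simulation with 20,000 runs, 45 patients, equal correlations, and one method shifted by 0.4 SD for power:

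| ρ | one-way type I error | repeated-measures type I error | one-way power | repeated-measures power |
|---|---|---|---|---|
| 0.3 | 1.6% | 5.2% | 44% | 63% |
| 0.5 | 0.3% | 5.0% | 41% | 79% |
| 0.7 | 0.01% | 4.8% | 36% | 95% |

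The direction is the same as for the two-sample test, and the type I error falls further below 5%.

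**The case against.** The best defence is that the trial is an ordinary three-arm parallel trial and that steps 2 and 3 loosely list what happens across the arms. The article calls the study a randomised trial, assigns participants to interventions, speaks of a study arm and of three groups, and names tests that suit independent groups. Neither step 2 nor step 3 says that each patient has all three methods. Step 6 and the mould comparison in {11a} do not help to decide, and the latter sits in background text.

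Much of this stands. A reader might infer that the trial is really within-patient; the documents do not support that, and they show only an unresolved contradiction. If the parallel reading is right, the named tests are suitable. Student's t-test could also be run paired, so only one-way ANOVA with Tukey is clearly an independent-groups method.

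Three other strong readings also fail:

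- *A mismatch would produce false positives.* With positive correlation it does the reverse.
- *Between-patient differences in defects would bias a parallel comparison.* Under randomisation they add noise, not bias.
- *Accuracy cannot be measured with one method per patient.* A condensed article may leave the software reference to the full protocol. The need for a reference is also not peculiar to parallel groups: three records of one defect compared with each other show agreement only.

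What the defence does not remove is the literal wording of steps 2 and 3, which stands in the operative methodology and is repeated in {33}.

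**Conclusion.** The contradiction is real and must be resolved. The criticism of the tests is conditional: it applies only if all three methods are recorded on each patient.

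In that case the unpaired analysis is conservative, with standard errors too large by about 20% to 83% for ρ from 0.3 to 0.7. The cost is a reduced chance of detecting a real difference in accuracy, for example about 20 percentage points of power at 0.5 SD and ρ = 0.5. These sizes rest on assumed correlations, equal variances and assumed effects, since the protocol gives none.

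A reader might set the difference detectable with 80% power within patients (0.43 SD, n = 45, ρ = 0.5) against that of a parallel trial (1.06 SD, assuming 15 per arm) and call the gap the size of the error. It is not. It compares two designs, and much of it comes from 45 rather than 15 observations per method: at ρ = 0, 45 per method already detects about 0.60 SD.

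**What to change.** Reconcile the methodology steps (Abstract, {9} and their repetition in {33}) with {20b}, so that they state how many methods each patient receives and what is randomised: the method, or the order of methods. Then match the analysis.

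- **If one method per patient:** reword steps 2 and 3 so that the defect is recorded and modelled by the allocated method, and keep the independent-groups tests.
- **If all three per patient:** replace one-way ANOVA with Tukey, and any unpaired t-test, in {14} and {20a}. Use a linear mixed model (method and order fixed, patient random) or repeated-measures ANOVA with paired comparisons.
- **Under either design:** name the reference surface from which deviation is measured, so that accuracy is distinguished from agreement between methods.

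If the design actually being run is kept, the cost is an amendment and analysis wording. Moving from parallel to within-patient is not a cheap change and is not recommended here as one. It would add a conventional impression and extra moulds for each patient, in a trial whose status section says recruitment began in September 2022. The article itself describes the conventional process as slow and uncomfortable for patients and aims to limit patient contact.

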**Discussion:**

Rodrigo Salazar-Gamarra1, Rosemary Seelaus, and Jorge Vicente Lopes da Silva et al., in the year 2016, discussed, as part of a method for manufacturing face prostheses utilising a mobile device, free software, and a photo capture protocol, that 2D captures of the anatomy of a patient with a facial defect were converted into a 3D model using monoscopic photogrammetry and a mobile device. The visual and technical integrity of the resulting digital models was assessed. The technological approach and models that resulted were thoroughly explained and evaluated for technical and clinical value.

Marta Revilla-León, Wael Att, and [name] et al. (2020) used a coordinate measuring equipment which was used to assess the accuracy of complete arch implant impression processes utilising conventional, photogrammetry, and intraoral scanning.

Corina Marilena Cristache and Ioana Tudor Liliana Moraru et al. in the year 2021 provided an update on defect data acquisition, editing, and design using open-source and commercially available software in digital workflow in maxillofacial prosthodontics.

This research looked at randomised clinical trials, case reports, case series, technical comments, letters to the editor, and reviews involving humans that were written in English and included detailed information on data acquisition, data processing software, and maxillofacial prosthetic part design.

**Trial registration:**

CTRI/2022/08/044524. Registered on September 16, 2022

**Supplementary Information:**

The online version contains supplementary material available at 10.1186/s13063-022-07005-1.

## Introduction

### Background and rationale {6a}

#### Background

Facial mutilation and deformities can be caused by cancer, tumours, injuries, infections, and inherited or acquired deformities and has the potential to degrade one’s quality of life by interfering with fundamental tasks like communication, breathing, feeding, and aesthetics.

Depending on the type of defect, producing maxillofacial prostheses for the rehabilitation of patients with various defects can be challenging and complex. The prosthesis is used to replace missing or damaged parts of the cranium and face, like the nose, auricle, orbit, and surrounding tissues, as well as missing areas of soft and hard tissue, with the primary goal of increasing the patient’s quality of life by rehabilitating oral functions such as speech, swallowing, and mastication.

Traditional maxillofacial prosthesis impression and fabrication processes include a number of complicated steps that are costly, time-consuming, and uncomfortable for the patient. These rely on the knowledge of the maxillofacial team, dental clinicians, and maxillofacial technician [1].

The foundation of the impression is the keystone for creating a prosthesis. However, this is the most time-consuming and difficult chair-side operation in maxillofacial prosthesis manufacturing since it requires prolonged interaction with the patient. The field of prosthesis fabrication is being transformed by the digital revolution. Digital technology allows for more accurate impression data to be gathered in less time (3 to 5 min) than traditional methods, lowering patient anxiety. Digital impressions eliminate the need for messy impression materials and provide patients with a more pleasant experience [1]. This method bypasses the procedure of traditional gypsum model fabrication. This eliminates the disparity caused by a dimensional distortion of the impression material and gypsum setting expansion. Traditional dental impression processes leave enough room for errors, such as voids or flaws, air bubbles, or deformities. While current technology for prosthesis planning has emerged as an alternative means to improve patient acceptability and pleasure, not only because the end result is a precisely fitted restoration but also because the chair-side adjustments required are reduced [2].

#### Rationale

The most frequent approaches for creating 3D virtual models are the following. To begin, 3D scanning is employed, in which the subjects are scanned in three dimensions, and the point cloud data is used to create a virtual digital model. The most difficult and time-consuming procedure in maxillofacial prosthesis is making an impression of the abnormality. Digital scanning is vital for achieving minimal interaction with the patient, and it avoids manual manufacture of the cast, resulting in no dimensional deformation of the cast.

In this COVID era, less interaction between patient and physician means a reduced danger of disease transmission. The photogrammetric method can be utilised as a first step toward obtaining a precise 3D representation of a defect that is acceptable for low-cost implementation.

### Objectives {7}

To assess and evaluate the conventional method of craniomaxillofacial impression proceduresTo assess and evaluate the photogrammetric method of craniomaxillofacial impression proceduresTo assess and evaluate the 3D scanning method of craniomaxillofacial impression proceduresTo compare the conventional, photogrammetry, and extraoral 3D scanning accuracy of craniofacial and midfacial impression procedures evaluated with a software

### Trial design {8}

The randomised control trial will be conducted at the Department of Prosthodontic, Sharad Pawar Dental College, in an isolated setup. The study protocol will be explained to the participating patients. Furthermore, a written informed consent will be obtained from their parents**.**

## Methods: participants, interventions and outcomes

### Study setting {9}

The study will be conducted at the Department of Prosthodontics Crown and Bridge Sharad Pawar Dental College and Hospital DMIMSU Sawangi Meghe Wardha.

Methodology:Patient screening will be done and the patient will be allocated to three techniques that are conventional manual method, photogrammetry method, and 3D scanning in a randomised mannerThe impression of the defect will be recorded by conventional manual method, photogrammetry method, and 3D scanningThe defect will be modelled in three ways: first is as per the manual dimension taken on patient, second is the organisation of photographic image taken with lab standards and third is plotting of point cloud data to generate the virtual 3D modelFor Photogrammetric prosthesis design: Finite photos/images will be taken at multiple angles to model the 3D virtual design. With the use of minimum photographs, the 3D modelling can be performed by using freeware, and a mould is obtainedThe CAD software was used to design the prosthesis, and the final negative mould can be printed using additive manufacturingThe mould fabricated by all three methods will be analysed by a software using reverse engineering technology

[figure not shown]

### Eligibility criteria {10}

Defect size not bigger than 9 × 12 cm (3.5 × 4.5 inches)In the age group of 10–70 yearsExtra oral defects

### Who will take informed consent? {26a}

Informed consent or assent from potential trial participants or authorised surrogates will be taken by the primary investigator

### Additional consent provisions for collection and use of participant data and biological specimens {26b}

Additional consent provisions for collection and use of participant data and biological specimens in ancillary studies will be taken by the primary investigator.

